### Recruitment

Study participants will be recruited through:

1 Notices posted on the Chung-Ang University Hospital bulletin boards2 Department of Physical and Rehabilitation Medicine outpatient clinic of the Chung-Ang University Hospital3 Notices posted on the bulletin boards of the Korean Parkinson’s Disease Association.

Eligibility to participate in the study will be determined by the research investigators based on the predefined criteria. Participants will be informed about the current treatment guidelines for mobility function in patients with Parkinson’s disease, as well as the potential benefits and risks associated with this study.

### Statistical methods

Demographic and clinical characteristics will be summarized using frequencies and percentages for categorical variables and means with standard deviations (SD) for continuous variables. The Shapiro–Wilk test will be used to assess the normality of continuous variables. To compare baseline characteristics between the intervention and control groups, an independent t-test will be applied for normally distributed variables, while the Mann–Whitney U test will be used for non-normally distributed variables.

All participants who undergo the intervention will be included in the intention-to-treat (ITT) population, which will also serve as the basis for safety analyses. Participants in the ITT population who complete both baseline and post-intervention assessments will comprise the full analysis set (FAS). Efficacy analyses will be conducted based on the FAS.

For efficacy analyses, the normality of outcome variables will be assessed using the Shapiro–Wilk test. Baseline characteristics will be included as covariates for adjustment in the statistical models. Additionally, comparisons between the robot (intervention) and control groups under each condition will be performed using either the independent t-test or the Mann–Whitney U test, depending on the distribution of the data. To compare post-intervention outcomes between the groups while adjusting for baseline values, analysis of covariance (ANCOVA) will be used. The post-intervention measurement will be the dependent variable, group assignment the independent factor, and the baseline measurement of the outcome will be included as a covariate. This approach accounts for any baseline imbalances and increases statistical power. Assumptions of normality and homogeneity of regression slopes will be assessed prior to analysis. Statistical significance will be set at a two-sided *p*-value of <0.05 for all analyses.

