
**Figure 1 fig1:**
[figure not shown]
The cable-driven soft wearable robot suit (H-Medi), showing key components such as including main unit (black boxes), sensors (yellow boxes), straps (green boxes), and directions of applied forces (red boxes).

The criteria for discontinuing the intervention are as follows:

1 Voluntary withdrawal by the participant.2 Missing a total of 3 out of 12 intervention sessions.3 Consecutively missing 2 intervention sessions.4 Discontinuation due to significant adverse events.5 Research investigator’s judgment that the continuation of the intervention is unsuitable.

The rehabilitation exercise session has been established as effective for patients with PD, regardless of the use of the soft wearable robot. Therefore, participants will be informed that assignment to either study group may not adversely affect their physical impairments or functional levels during the intervention period. Additionally, since all interventions will take place within the hospital, research coordinators will maintain periodic contact with participants via phone calls to remind them of upcoming interventions.

Participants will maintain their usual dosage of medication for their underlying conditions, including PD. Beyond the exercise intervention implemented in this study, any additional physical activities conducted at medical centers, including rehabilitation centers, are prohibited.

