### Sample size

The primary outcome of this study is the change in gait speed between T0 and T1, which has been widely used in previous studies (9). The power of the study (1–*β*) was set at 80%, with a significance level (*α*) of 5%. The required sample size was calculated using Lehr’s formula (55). The clinically significant effect size (*δ*) was been designated as 0.18, with an expected standard deviation (*σ*) of 0.17 (22, 38). Considering an anticipated follow-up rate of 80%, the final calculated sample size was 17 participants per each group, totaling 34 participants.

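### All efficacy analyses rest on a complete-case set labelled FAS, drawn from a treated set labelled ITT, so the primary comparison may be biased if loss depends on outcome; size and direction are unknown

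*Protocol article*

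**What the plan says.** Three statements in the Statistical methods section of the protocol article fix the populations:

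- "All participants who undergo the intervention will be included in the intention-to-treat (ITT) population". This set is also the basis for safety.
- "Participants in the ITT population who complete both baseline and post-intervention assessments will comprise the full analysis set (FAS"). So this second set is a subset of the first.
- The third statement settles which of the two carries the results: "Efficacy analyses will be conducted based on the FAS".

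The section names no efficacy analysis on a wider set.

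Other sections bear on who ends up in the FAS:

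- **Sample size** plans for loss: "Considering an anticipated follow-up rate of 80" per cent, giving 17 per group and 34 in total.
- **Interventions** (list after Figure 1) gives five reasons for stopping the intervention: voluntary withdrawal; "Missing a total of 3 out of 12 intervention sessions"; two missed sessions in a row; significant adverse events; and investigator judgment.
- **Outcomes** places T1 within 7 days of the final intervention session. The article states no T1 for a participant who stops early.
- **Table 1** puts group assignment at baseline, and **Participant timeline** starts training within 7 days of the baseline evaluations.
- **Trial design** says that allocation follows the participant's choice of session time without randomisation, and that participants are not blinded.

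**The concern.** Neither label means what a reader will take it to mean. An intention-to-treat set contains everyone assigned, as assigned; here, anyone assigned who never starts is left out. A full analysis set is normally as close to that as possible; here it is the subset with both T0 and T1 observed.

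This matters for bias as well as for naming. Withdrawal, missed sessions, adverse events and investigator judgment can all relate to how a participant tolerates or responds to training. If such participants have no T1, they leave the efficacy analysis. The estimate then describes those who were assessed at the end, under labels that suggest all participants. The wording on T1 adds to the problem. If the final session means session 12, an early stopper has no T1. If it means the last session attended, T1 falls at a variable time after baseline.

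**Working it through.** **Inputs** (Sample size, Statistical methods and Trial design sections): δ = 0.18 and σ = 0.17; power 80%; "significance level (*α*) of 5" per cent, two-sided; 1:1 allocation; follow-up 80%. The article gives no unit for δ and σ. I take m/s, and I take σ as the SD of change.

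**1. The plan's own figure.** Lehr's formula: n = 16 × (0.17/0.18)² = 14.27 per group. Allowing for loss: 14.27/0.80 = 17.84 per group. The stated 17 is close to this; 14 × 1.2 = 16.8 rounds to it exactly. The sample size is not the issue here.

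**2. Size of the efficacy set.** 34 × 0.80 = 27.2 analysed, or 13.6 per group; 34 × 0.20 = 6.8 lost, about 7 participants. Power at 13.6 per group is 0.788 by the normal approximation and 0.756 by the t-test. The planned loss is therefore largely budgeted for in power, and the open question is bias.

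**3. When complete-case ANCOVA is safe.** The planned model regresses T1 on group and baseline gait speed, with further baseline characteristics as covariates. If the chance of a missing T1 depends only on arm and those covariates, the complete-case group effect is not biased by the loss. If it depends on the unobserved T1, or on tolerance that is itself related to T1 beyond baseline, the effect is biased.

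**4. Possible size.** In one arm let a fraction L be lost, and let those lost have a mean change kσ below that arm's completers, beyond what baseline explains. The mean for the whole arm is then the completers' mean minus Lkσ. With R for robot and C for control:

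bias in (robot − control) = σ × (L_R k_R − L_C k_C)

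The article gives no values of L or k by arm, so these are scenarios with L = 0.20 in both arms:

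| k in robot arm | k in control arm | Bias (m/s) | Share of 0.18 |
|---|---|---|---|
| 0 | 0 | 0 | 0% |
| 0.5 | 0 | +0.20 × 0.5 × 0.17 = +0.017 | +9% |
| 1 | 0 | +0.20 × 1 × 0.17 = +0.034 | +19% |
| 0 | 0.5 | −0.017 | −9% |
| 0 | 1 | −0.034 | −19% |
| 1 | 1 | 0.034 − 0.034 = 0 | 0% |

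**5. Effect on the test.** With 14 per group, σ = 0.17 and no true difference, the two-sided type I error of an unadjusted t-test is 0.057 at a bias of 0.017 and 0.080 at 0.034, against a nominal 0.05.

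**6. Would imputation remove this bias?** There are only two time points. Imputing T1 within arm from baseline uses the same regression of T1 on baseline, estimated in the same observed participants, as the complete-case ANCOVA. When loss depends on the unobserved outcome, both give essentially the same answer. Sessions attended would help as a predictor only if it predicts T1, and a model with several predictors fitted to about 14 observed participants per arm is fragile. What adds information is collecting T1. A delta adjustment shows how far the result depends on what was not collected.

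**The case against.** **The FAS requires two assessments, not completed training.** This stands. The Interventions list governs stopping the intervention; it does not say that a participant leaves the study or skips T1. Someone who stops early and attends T1 stays in the FAS. A reader might infer that poor tolerance or poor response automatically excludes a participant, or that the result covers only those who finished training. The text does not say so. What remains is that the article provides no T1 for such people, and expects one participant in five to be lost.

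**The suit is not said to cause discomfort or loss.** This also stands. The Introduction ties discomfort to rigid exoskeletons and presents soft devices as more comfortable. The Adverse events section lists musculoskeletal discomfort for the study in general. A reader might infer heavier loss in the robot arm from the worn device and the absence of participant blinding. But control participants, who also know their arm, could leave too, and that would push the bias the other way.

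**Post-discontinuation follow-up and missing-data methods are often left to a fuller document.** This is fair for the detail, and their absence is not the point. The populations and the efficacy set are stated here, and it is that stated rule which is at issue.

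**Without randomisation, an intention-to-treat set has little to preserve.** This stands in part. Analysing everyone as assigned cannot restore a comparability that session choice never gave. But selection after assignment is a second source of bias on top of selection at entry, and baseline adjustment need not remove it.

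**Few will be assigned and never treated.** This is probably true, since training starts within 7 days of baseline. Most of the exposure comes from the missing T1.

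**Conclusion.** The concern holds in a limited form. A treated set is labelled ITT and a complete-case subset is labelled FAS, and every efficacy analysis rests on that subset. About 7 of 34 participants are expected to be missing from it. The primary comparison may be biased if loss depends on outcome; if loss depends only on arm and the adjusted baseline covariates, it is not.

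Neither size nor direction can be read from the article. With 20% of one arm lost, those lost 0 to 1 SD worse than that arm's completers, and uninformative loss in the other arm, the bias is 0 to 0.034 m/s (0 to 19% of 0.18). It runs towards the robot arm or against it according to where the informative loss falls, and is near zero if loss is alike in both.

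A reader might go further and conclude that the suit's effect will be overstated, by about a third of the planned effect if the lowest fifth of robot-arm responders are the ones lost (0.35 × 0.17 = 0.0595 m/s, 33% of 0.18). The documents do not support that: they give no loss by arm or by reason, and an exact removal of the worst responders in one arm only is an extreme case.

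**What to change.** 1. Define the ITT/FAS as all participants assigned to an arm, analysed as assigned.
2. Seek T1 at the planned time (end of week 6, within 7 days) from everyone willing, including those who stop the intervention. This does most of the work: a T1 that is not collected cannot be recovered later.
3. Keep the baseline-adjusted ANCOVA as primary, on all assigned participants with an observed T1, and state its assumption that loss depends only on arm and the adjusted covariates.
4. Call the set as now defined a complete-case set.
5. Report loss by arm and by reason.
6. Add a delta-adjusted imputation as a sensitivity analysis, with shifts applied in either arm. Do not make multiple imputation primary: with T0 and T1 only, it would essentially reproduce the complete-case answer.

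The cost is wording, a few extra T1 visits and a little more analysis. The change reduces selection after assignment. It does not touch the confounding at entry that comes from allocation by session choice, and the report should say so.

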### Outcomes

Baseline evaluations (T0) will be conducted within 7 days before the initiation of the intervention. Post-intervention evaluations (T1) will be conducted within 7 days after the final intervention session.

The primary outcome will be the change in gait speed from T0 to T1. Gait speed will be measured as the average value from two trials of the 10-meter walk test. This test is sensitive to mobility impairment, predicts disability and falls, and is feasible for use in clinical settings, demonstrating both reliability and validity (37, 38).

The secondary outcomes will be the change from T0 to T1 of the following assessments: 4-meter walk test, TUG, Short Physical Performance Battery (SPPB), BBS, MDS-UPDRS, Freezing of Gait Questionnaire (FoGQ), gait parameters measured by an IMU sensor-based gait analysis system (Human Track, R. Biotech Co. Ltd., Seoul, Korea) (39) and the GAITRITE system (CIR Systems, PA, United States) (40), muscle strength and endurance measured by isokinetic dynamometer Biodex system (Biodex System 4, Biodex Medical Systems, Shirley, NY, United States) (41), thickness of quadriceps muscles measured by ultrasound, body composition measured by Dual-energy X-ray absorptiometry (DEXA) (42), cognitive function measured by Mini-Mental State Examination (MMSE), and depression measured by Beck Depression Inventory (BDI). In addition, questionnaires assessing comfort and usability, along with participants’ feedback, will be collected after the completion of the intervention sessions.

The TUG evaluates gait, balance, and fall risk. Participants will rise from a chair, walk 3 meters to a cone, turn, return to the chair, and sit down. Completion time (seconds) will be recorded (43). The SPPB will assess balance, walking ability, and transfers. Each component is scored on a 0–4 scale, with a total score ranging from 0 to 12, where higher scores indicate better performance. The BBS assesses functional standing balance through 14 tasks of increasing difficulty, including sitting, standing, single-leg stance, and positional changes. Each item is scored on a 0–4 scale, with a maximum total score of 56, where higher scores indicate better balance ability (44).

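### The single primary outcome is analysed both by an unadjusted t-test or Mann-Whitney test and by baseline-adjusted ANCOVA, and neither is named as the deciding analysis

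*Protocol article*

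**What the plan says.** The Outcomes section is clear about the endpoint: "The primary outcome will be the change in gait speed from T0 to T1", measured by the 10-metre walk test.

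The Statistical methods section then sets out, for the efficacy analyses together:

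- a Shapiro-Wilk test of the outcome variables;
- a sentence that baseline characteristics will enter the models as covariates, without listing them;
- a further statement that "comparisons between the robot (intervention) and control groups under each condition will be performed using either the independent t-test" or the Mann-Whitney test, depending on the distribution. It does not say whether the variable compared is the change or the T1 value. It also refers to conditions, although this is a two-arm parallel design with one post-intervention visit;
- a baseline-adjusted model: "To compare post-intervention outcomes between the groups while adjusting for baseline values, analysis of covariance (ANCOVA) will be used". The dependent variable is the T1 measurement and the covariate is its baseline value. "Assumptions of normality and homogeneity of regression slopes will be assessed prior to analysis", but the text does not say what follows if a check fails.

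One threshold covers everything: "Statistical significance will be set at a two-sided *p*-value of <0.05 for all analyses". No sentence ranks these analyses.

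The Trial design section adds that allocation is by self-selected session time without randomisation, and that appropriate adjustments will be made for baseline differences.

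**The concern.** A single primary outcome should have a single deciding analysis. Here the text supports two that are not equivalent. One is unadjusted, and moves between a comparison of means and a comparison of ranks according to a test on the same data. The other is adjusted for baseline.

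Two things are at stake. First, if either result may carry the conclusion, the chance of a false positive exceeds the stated 5%. Second, the two analyses answer the same question only when the arms are alike at baseline. In a randomised trial that holds on average. In this trial participants choose their session time, and the protocol itself concedes possible selection bias and confounding. If the arms differ at baseline, the analyses target different quantities and can point in different directions.

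**Working it through.** **The plan's own figure.** The Sample size section states: "The required sample size was calculated using Lehr’s formula (55". The effect "was been designated as 0.18, with an expected standard deviation" of 0.17, with 80% power and 5% significance. Lehr's formula gives 16 × (0.17/0.18)² = 14.27 per group, and 14.27/0.8 = 17.84 after allowing for 80% follow-up. The stated 17 per group is within rounding of this, and 17 × 0.8 = 13.6, so about 14 completers per arm. The formula is for an unadjusted comparison of two means, so the sample size does not point to ANCOVA as the deciding test.

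**Inputs to the simulation.** From the documents: 14 completers per arm, SD 0.17, difference 0.18, two-sided 0.05. Assumed: 0.17 is the SD of the change (the text does not say), data are bivariate normal with equal variances, and the T0-T1 correlation r is 0.5, 0.7 or 0.85 (not given). The arms have no systematic baseline difference. The unadjusted test follows the plan's rule: t-test unless Shapiro-Wilk rejects in either arm, otherwise Mann-Whitney. There were 10,000 trials per setting with no effect and 4,000 with an effect of 0.18.

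| | r = 0.5 | r = 0.7 | r = 0.85 |
|---|---|---|---|
| **No effect** | | | |
| Change test significant | 4.9% | 5.3% | 5.2% |
| ANCOVA significant | 5.0% | 5.0% | 5.4% |
| Either significant | 7.3% | 6.9% | 6.7% |
| Either, or the same rule on T1 | 9.7% | 10.0% | 10.7% |
| Change test and ANCOVA disagree | 4.8% | 3.6% | 2.7% |
| **True difference 0.18** | | | |
| Power, change test | 75.5% | 77.8% | 77.6% |
| Power, ANCOVA | 85.6% | 82.9% | 79.2% |
| Change test and ANCOVA disagree | 14.9% | 10.5% | 7.8% |

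Repeat runs gave similar results: about 7% for either test, 9 to 12% with T1 added, disagreement of 3 to 4% and 8 to 13%, and power of about 77% against 79 to 85%.

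The power gap has a simple source. With equal variances, the ANCOVA residual SD is 0.17 × √((1 + r)/2). This is 0.147 at r = 0.5 and 0.157 at r = 0.7, against 0.17 for the change.

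**Baseline imbalance.** Let B be the baseline difference between arms, D the T1 difference, and b the slope of T1 on baseline. The change-score estimate is D − B and the ANCOVA estimate is D − bB, so they differ by (1 − b)B. For an assumed B = 0.10 m/s and b = 0.7, that is 0.3 × 0.10 = 0.03 m/s, or one sixth of the planned 0.18. Which estimate is unbiased depends on how the imbalance arises:

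- If the arms' difference shrinks along the slope (D = 0.07 with no effect), change gives 0.07 − 0.10 = −0.03 and ANCOVA gives 0.07 − 0.07 = 0.00.
- If the difference is stable (D = 0.10 with no effect), change gives 0.00 and ANCOVA gives 0.10 − 0.07 = +0.03.

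The documents do not establish which applies.

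**The case against.** The best defence is that ANCOVA is plainly meant to lead. It is the only analysis with a stated dependent variable, factor, covariate and rationale, and the t-test sentence is introduced as an addition. The Trial design section also promises adjustment, which an unadjusted test cannot deliver. That is a fair reading of the likely intention. It does not settle the matter: the text never says so, applies one threshold to all analyses, and sizes the trial with an unadjusted formula. Nor is this a detail left to a fuller document, because the article itself fixes several analyses for one outcome without ranking them.

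The analysts are also to stay blinded until the final analyses are complete. That helps, but a two-sided p-value looks the same whichever arm carries which label, so blinding does not decide which test counts.

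Some stronger readings are tempting and should be resisted:

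- *There are three tests, so error is 10% or more.* The text lists one unadjusted comparison plus ANCOVA. A third test arises only if the unadjusted one is run on both change and T1. The silence on the variable permits this, but the text does not plan it.
- *Error is far higher under baseline imbalance.* Rejection rates then mix bias from non-equivalent groups, which the protocol discloses, with the effect of choosing between tests.
- *ANCOVA is the unbiased choice here.* The two cases above show that this depends on an unverified assumption.
- *The Shapiro-Wilk switch inflates error.* In the simulation the rule alone holds 4.9 to 5.3%. The objection to it is that it changes the question from means to ranks.

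**Conclusion.** The point holds, at moderate weight: it should be fixed, but it does not by itself invalidate the trial. The plan leaves two non-equivalent tests of its only primary outcome with equal standing, so the conclusion can depend on which is reported, although in most trials they would agree.

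With balanced arms, allowing either to decide raises type I error from 5% to about 7%, or to about 9 to 12% if the unadjusted test may also be run on T1. At the planned effect, power is about 75 to 78% for the change test and 79 to 86% for ANCOVA. With imbalance, the two estimates separate by (1 − slope) times the baseline difference.

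These sizes rest on the assumed correlation, on normality and on reading 0.17 as the SD of change. The 0.03 m/s illustration rests on an assumed imbalance and slope. That no analysis is named as deciding rests on the text alone.

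**What to change.** In the Statistical methods section:

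1. Name one primary analysis: ANCOVA of T1 10-metre gait speed on arm and baseline gait speed, reporting the adjusted mean difference with its 95% confidence interval. This gives the same arm effect as ANCOVA of the change with baseline as covariate, so it agrees with the endpoint in the Outcomes section.
2. State a short, fixed list of any further baseline covariates, or state that there are none. The primary model then agrees with the existing covariate sentence and with the adjustment promised under Trial design.
3. Remove the Shapiro-Wilk switch for the primary outcome, and delete the reference to conditions.
4. Label the t-test, Mann-Whitney and change-score comparisons as sensitivity analyses, and state the variable each one uses.

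Naming ANCOVA settles which result decides. It does not remove confounding from self-selected allocation, so the change-score result should be shown beside it as a sensitivity analysis. The cost is a few sentences, with no extra patients, data or change to the stated sample size. It should be done before any outcome comparison between the groups is seen.

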## Methods

### Trial design

This is a prospective, single-center, single-blind, parallel-group trial. Participants will be assigned to two groups, in a 1:1 ratio: the robot group and the control group. The intervention session times will be pre-assigned as either robot or control sessions, with an equal number of slots for each group. Participants will then select their preferred session time according to their personal schedules, without knowing which sessions are designated as robot or control. Their group allocation will be determined based on this selection. As randomization is not employed and group assignment is based on self-selection, potential selection bias and confounding may occur. However, since session times for both groups are evenly distributed and baseline demographic and clinical characteristics of participants will be collected, we suggest that potential bias can be minimized. In the analysis of study results, we will apply appropriate statistical adjustments for any baseline differences. One research investigator will manage the session schedule and contact participants. This investigator, physical therapists conducting the intervention, and the participants will not be blinded to group assignments. All other investigators including outcome assessors, investigators involved in data interpretation and analyses, and the principal investigator (PI) will remain blinded throughout the study. Group assignments will be unblinded only after completion of the final statistical analyses, or during the study if a serious adverse event occurs, with the approval of the PI.

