### Interventions

The participants will receive a 45-min rehabilitation exercise intervention session consisting of 20-min of strength training, a 5-min rest period, and 20-min of treadmill walking. Strength training will be conducted in a one-on-one setting with a skilled physical therapist and included hamstring and quadriceps stretching, one-leg bridging, hip abductor strengthening, quadriceps strengthening, bird-dog exercises, squatting, and one-leg standing exercises. During the treadmill walking session, participants were secured with a harness to ensure safety and walked at an individually self-selected speed within target of a moderate intensity range (Borg Rating of Perceived Exertion scale, RPE 11–13). The rehabilitation exercise program will be applied identically to all participants. The only difference between the two groups will be whether participants wear the soft wearable robot suit during the 20-min treadmill walking session. The intervention will be conducted 2 times per week, a total of 12 sessions for 6 weeks. We will review each participant’s medication schedule to determine their PD medication on/off periods. The intervention will be conducted during the “on” periods for each participant.

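### The arm follows from the session time a participant picks, and an even spread of times is offered as a safeguard against bias, yet no stated analysis conditions on session time

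*Protocol article*

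**What the plan says.** The Trial design section of the protocol article describes the allocation in two steps. First, "The intervention session times will be pre-assigned as either robot or control sessions, with an equal number of slots for each group". Second, "Participants will then select their preferred session time according to their personal schedules, without knowing which sessions are designated as robot or control". The choice of time decides the group.

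The same section is open about the weakness: "As randomization is not employed and group assignment is based on self-selection, potential selection bias and confounding may occur". It then gives two grounds for expecting the bias to be small, "since session times for both groups are evenly distributed and baseline demographic and clinical characteristics of participants will be collected", and promises that "we will apply appropriate statistical adjustments for any baseline differences".

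The Interventions section ties session time to treatment of the disease. Staff review each participant's "medication schedule to determine their PD medication on/off periods", and sessions are held in on periods.

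The Statistical methods section specifies an ANCOVA with the post-intervention value as dependent variable, "group assignment the independent factor, and the baseline measurement of the outcome will be included as a covariate". Another sentence there says that baseline characteristics will be adjusted for in the models, but lists none. Unadjusted t-tests or Mann-Whitney tests are also planned. Session time, part of day and slot are in none of these analyses.

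**The concern.** In this design, session time plays the part that a randomization list would otherwise play. The first safeguard concerns the times that are offered. The comparison depends on the times that are taken. Equal numbers of robot and control slots on the calendar do not guarantee that the two groups who enrol are alike in when they attend.

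This matters only if the time chosen is related to outcome. The article gives two reasons why it might be. People choose by personal schedule, which may reflect work, support at home or fatigue. Sessions must also fall in an on period, so the feasible times depend on the medication schedule. Baseline gait speed need not capture either.

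If the robot and control groups differ in their mix of session times, and the mix is prognostic, part of the estimated robot effect is a time-of-day effect. It could go in either direction. Comparing the arms within the same part of the day would remove that part, but no stated model does so.

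**Working it through.** **Inputs from the article (Sample size section).** Effect 0.18 and SD 0.17 (units not printed; m/s assumed), 80% power, 5% significance, 80% follow-up, 17 per arm.

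**The plan's own figure.** Lehr's formula gives 16 × (0.17/0.18)² = 14.27 per arm. Dividing by 0.8 gives 17.84. The stated 17 is close to this; 14/0.8 = 17.5 rounded down gives it exactly. Taking 17 as stated, the expected completers are 17 × 0.8 = 13.6 per arm.

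**Bias (assumptions, not in the documents).** Suppose two blocks, morning and afternoon, with 65% of robot and 35% of control participants in the morning. Suppose also that, after adjustment for baseline gait speed, the blocks differ by 0.05 to 0.10 m/s.

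Bias = (difference in block share) × (difference in outcome between blocks)

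- Low: 0.30 × 0.05 = 0.015 m/s; 0.015/0.18 = 8%.
- High: 0.30 × 0.10 = 0.030 m/s; 0.030/0.18 = 17%.

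With 14 completers per arm the standard error is 0.17 × √(2/14) = 0.064. A systematic shift of 0.015 to 0.030 moves the two-sided type I error from 0.050 to about 0.056 to 0.075 (normal approximation).

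**Price of adjusting.** With equal arms and shares of 65% and 35%, the block-arm correlation is 0.30/(2 × √(0.5 × 0.5)) = 0.3. The variance of the arm contrast is multiplied by 1/(1 − 0.3²) = 1.099. Using a t-test approximation with 13.6 per arm, SD 0.17, and no credit for any outcome variance that the block explains:

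| Model | Power for 0.18 |
|---|---|
| No block term | 0.756 |
| Block term, correlation 0.1 | 0.751 |
| Block term, correlation 0.3 | 0.715 |

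The loss is about 4 points at 0.3 and under 1 point at 0.1. If labels are balanced within blocks and choice is unrelated to arm, the correlation should usually be small and the cost slight.

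**The case against.** **The adjustment may already be covered.** It would be wrong to say that the plan adjusts for baseline gait speed alone. The Statistical methods section also adds baseline characteristics, the Trial design section promises adjustment for baseline differences, and the choice of covariates can be left to an analysis plan. This stands in part. However, session time is an allocation variable and not clearly a demographic or clinical characteristic, so neither sentence commits the trial to using it.

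**Participants do not know the labels, and the on-period rule applies to everyone.** This is the strongest reply. Not knowing the labels prevents anyone from choosing an arm, and a rule common to both arms does not by itself tie prognosis to arm. A systematic split such as 65/35 needs the labels to line up with popular times, and nothing in the article shows that they do. If choice really is unrelated to arm, an uneven split is ordinary chance imbalance. It is already reflected in the residual variance, and type I error stays at 0.050. So the bias is possible but not demonstrated. The article does not report a layout by part of day that would rule it out.

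**Clustering.** A reader might infer that participants share slots, so that the ANCOVA standard errors are too small. The documents do not support this. They nowhere say that a slot or a therapist serves several participants, and strength training is one-on-one. With one participant per slot the design effect, 1 + (m − 1) × ICC, is 1 and nothing changes. If slots did serve two participants each, an assumed ICC of 0.05 to 0.20 would give a type I error of 0.056 to 0.074, but both figures are conjecture.

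**Conclusion.** The point holds as a modest, inexpensive improvement. The article rests part of its bias argument on the even spread of session times and then specifies an analysis that makes no use of session time. An even spread of offered slots does not guarantee one of chosen slots, and the time chosen may be prognostic.

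The illustrative bias of 0.015 to 0.030 m/s depends wholly on an assumed 30-point difference in block share and an assumed 0.05 to 0.10 m/s difference between blocks. Smaller values shrink it in proportion, and either being zero removes it. It is too small to account for an effect near 0.18, but it could matter for a borderline result in a trial of 34. The documents do not support the stronger conclusions that the estimate is known to be biased or that the standard errors are wrong.

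**What to change.** 1. Make sure that each part-of-day block (for example morning and afternoon) contains both robot and control slots, and state the layout. A block with one arm only gives no within-block comparison.
2. Record each participant's block in the eCRF and report block by arm with the baseline characteristics.
3. Add block as a fixed factor to the primary ANCOVA, beside group and baseline gait speed, and name it in the text before group assignments are unblinded.
4. Do not fit the individual slot as a fixed effect. Each slot belongs to one arm, so slot is aliased with arm.
5. Only if slots or therapists turn out to serve several participants, add a sensitivity analysis with a random slot effect or a small-sample cluster-robust standard error.

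**Cost.** One eCRF field, one model term and one degree of freedom with two blocks, plus the power loss shown above. Balancing labels within blocks also changes the scheduling procedure, unless the present calendar already does this. If the calendar can no longer be changed, steps 2 and 3 remain possible. Adjustment for block removes bias from differences between blocks only. Self-selection within a block remains, and the report should say so.
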